#### Handling of dropouts

2.2.3

(1) Criteria for dropout

Patients who have provided informed consent, been screened and randomized for the trial, but for any reason do not complete the treatment and observation period as outlined in the study protocol will be considered dropouts.

(2) Handling of dropout cases

1) After a patient drops out, the researcher should contact the patient via home visits, scheduled follow-ups, phone calls, or letters to inquire about the reason for dropout, record recent sleep patterns, and complete any assessments that can be performed.

2) For patients who drop out due to allergies, adverse reactions, or treatment ineffectiveness, appropriate treatment measures should be taken according to their condition.

3) All dropout cases should be properly documented, both for archival purposes and for the required analysis in statistical evaluation. No additional patients will be recruited to replace dropouts.

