#### Trial termination

2.2.4

(1) If a serious adverse event occurs, or the researcher determines the trial should be stopped for this reason.(2) If the patient’s condition worsens, or if other issues arise during the trial that affect observation, the researcher may decide to stop the trial.(3) If significant protocol deviations occur during the implementation of the clinical trial, such as poor adherence to the protocol, making efficacy evaluation difficult, the trial may be stopped.(4) If the participant expresses unwillingness to continue with the trial and requests to withdraw.

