### Safety evaluation

2.10

All participants will undergo a safety evaluation before and after treatment. Adverse events (e.g., localized skin redness, swelling, itching) that occur during treatment will be recorded. In case of an adverse event, the cause will be determined, its correlation with AA treatment will be assessed, and symptomatic treatment will be provided. In addition, all participants will undergo professional depression assessment, and depressive symptoms will be recorded on the Case Report Form (CRF). If severe depression is detected, the trial will be terminated, and further treatment will be provided.

Safety will be evaluated according to the following adverse reaction grading system: Grade 1: Safe, no adverse reactions; Grade 2: Generally safe, mild adverse reactions that do not require treatment and allow continuation of therapy; Grade 3: Safety concerns, moderate adverse reactions, treatable but continuing therapy allowed; Grade 4: Trial termination due to adverse reactions.

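### The four-grade safety scale in section 2.10 mixes severity with action taken, so Grade 4 pools mild, moderate and severe reactions that lead to stopping

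*Protocol article*

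**What the plan says.** Section 2.10 of the protocol article introduces the scale as the basis of the safety assessment: "Safety will be evaluated according to the following adverse reaction grading system". Grade 1 is the absence of any reaction. The next grade is "Grade 2: Generally safe, mild adverse reactions that do not require treatment and allow continuation of therapy". The last two are "Grade 3: Safety concerns, moderate adverse reactions, treatable but continuing therapy allowed; Grade 4: Trial termination due to adverse reactions".

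The same section deals with recording: "Adverse events (e.g., localized skin redness, swelling, itching) that occur during treatment will be recorded". It adds that the cause and the relation to auricular acupressure (AA) are assessed, and that in case of an adverse event "symptomatic treatment will be provided". That promise is not limited to any level of severity.

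Stopping is covered in section 2.2.4, which leaves it to a serious adverse event, the researcher's judgement or the participant's request. Section 2.2.3 requires researchers to ask dropouts for their reason and to document it. No section gives a severity scale other than the one in 2.10.

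**The concern.** A grade that is used to compare safety between arms should mean the same thing at each step. Here Grades 2 and 3 describe how bad a reaction was, along with its management, while Grade 4 describes only what was done about it. Once a participant stops because of a reaction, the grade no longer shows whether the reaction was mild itching or something severe.

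This matters most for AA against sham auricular acupressure (SAA). The AA arm presses beans on the ear (2.7.2) and the SAA arm presses tape without seeds (2.7.3), so local skin reactions could plausibly differ. The Introduction includes safety in the aim of the study. If Grade 4 is more frequent in one arm, a reader cannot tell from the grades whether that arm had worse reactions or only a lower threshold for stopping.

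**Working it through.** There is no figure to reproduce, so the check sets the definitions in 2.10 against each combination of severity, need for treatment and action.

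**Inputs, all from 2.10**
- Grade 1: no reaction.
- Grade 2: mild, treatment not required, therapy continues.
- Grade 3: moderate, treatable, therapy continues.
- Grade 4: termination because of adverse reactions, with no severity term.

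**Mapping on the literal wording**

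| Severity | Continues, no treatment required | Continues, treatment required | Stops because of the reaction |
|---|---|---|---|
| Mild | Grade 2 | Not clearly Grade 2 or 3 | Grade 4 |
| Moderate | Grade 3 | Grade 3 | Grade 4 |
| Severe | No grade | No grade | Grade 4 |

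The moderate row reads treatable as capable of being treated.

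**Step 1, last column.** All three severities give Grade 4, so severity cannot be recovered from the grade for anyone who stops because of a reaction.

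**Step 2, consequence for a comparison of arms.** Suppose two arms each have *m* moderate reactions. In the first, *s* of them lead to stopping; in the second, none do. The first arm shows *m* − *s* at Grade 3 and *s* at Grade 4; the second shows *m* at Grade 3 and 0 at Grade 4. The grades differ although severity is identical. Conversely, *s* mild reactions leading to stopping in one arm and *s* severe ones in the other both appear as *s* at Grade 4. The grades agree although severity differs.

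**Step 3, mild with treatment required.** This is not Grade 1, because a reaction occurred. It fails the Grade 2 condition that no treatment is needed. Grade 3 says moderate. Grade 4 requires termination. Since 2.10 offers symptomatic treatment for adverse events in general and gives redness, swelling and itching as examples, the case is realistic. A mild reaction treated only as a courtesy is different: treatment was given but not required, so it remains Grade 2.

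**Step 4, severe with continuation.** This has no grade either. It is unlikely with local ear reactions, and 2.2.4 gives the researcher discretion: "if other issues arise during the trial that affect observation, the researcher may decide to stop the trial". The point does not rest on it.

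**The case against.** The best defence is that this is not a severity scale at all. Grade 1 cannot grade an event, so the scale looks like an overall rating per participant, ordered by consequence: none, tolerated, needing management, stopped. In such a rating, stopping belongs at the top whatever the symptoms. That is a coherent convention, but the scale does not follow it cleanly, because Grades 2 and 3 bring in mild and moderate. Even as an overall rating, Grade 4 pools severities, and nothing else in the article supplies the missing severity.

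The second defence is that need for treatment is what separates Grade 2 from Grade 3, so a mild reaction needing treatment simply goes to Grade 3. That is a fair reading and is why the point is secondary. The wording does not settle it, since Grade 3 says moderate. A reader might go further and infer that any treated mild reaction has no grade. The text does not support that: Grade 2 turns on whether treatment is required, not on whether it was given.

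A reader might also infer that Grade 4 is ambiguous, because 2.2.4 lists under the same heading as the other termination rules "If the participant expresses unwillingness to continue with the trial and requests to withdraw". This does not hold up well. Grade 4 requires that the reaction be the cause, so a participant who leaves because of itching meets it and one who leaves for another reason does not. The same person can be Grade 4 and also a withdrawal on request. Section 2.2.3 supplies the evidence needed: "All dropout cases should be properly documented, both for archival purposes and for the required analysis in statistical evaluation".

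Finally, adverse events are recorded in any case, and the article does not say that grade counts will be the only safety summary or plan a test of them between arms. That stands and keeps the priority low. It does not remove the point, because the article sets out the scale in full and makes it the stated basis of the safety evaluation.

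**Conclusion.** The point holds in a limited form. As defined, Grade 4 loses severity for every reaction that leads to stopping, and grade counts by arm mix severity with the decision to stop. This follows from the wording alone. The lack of a clear place for a mild reaction needing treatment is a lesser weakness, which depends on how the boundary between Grades 2 and 3 is read.

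No size in participants can be given, because the article states no reaction or stopping rates, and a count of definitional combinations would say nothing about frequency. The conclusion assumes that the four grades are used as written and that no separate severity field exists in documents not shown. It concerns the safety tabulation only and is a cheap improvement.

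**What to change.** In 2.10, replace the grades with wording such as:

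> *Each adverse event will be graded by severity alone (mild, moderate, severe). Whether treatment was required (yes or no) and the action taken with the ear intervention (continued, interrupted, stopped) will be recorded as separate fields. Severity, and stopping due to adverse events, will each be reported by arm.*

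If the team prefers to keep the four-grade overall rating, two changes are enough: word Grade 3 as mild or moderate, requiring treatment, therapy continued; and report each Grade 4 case with its severity. Under that wording a moderate reaction that needs no treatment also has to be placed, most simply by extending Grade 2 to any mild or moderate reaction that needs none.

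The cost is one revised paragraph and a few fields on the adverse-event page of the case report form. Participants already graded would need severity assigned from their existing records, which is less reliable than grading at the time, so the change is best made early. Decisions on treating or stopping stay as they are, and no visits, staff or efficacy analyses are added.

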### Quality control

2.11

The acupressure beans and adhesive tapes used in the study were uniformly provided by the researchers to ensure standardized specifications. Prior to implementation, all physicians administering the interventions practiced accurate localization on a simulated ear model and were provided with an annotated acupoint diagram to guide proper technique.

The PSQI, BDI, ASHS, ASWS, CDI and ASLEC scales will be assessed for completion eligibility by a professionally qualified physician. Prior to the start of the study, researchers will undergo training on the trial protocol, undergo consistency checks on symptom quantification standards, and sign a researcher declaration. Researchers strictly adhered to informed consent procedures to ensure participants fully understood trial requirements and provided comprehensive cooperation. For consented participants, paper-based questionnaires were distributed, and parents/guardians were contacted to facilitate questionnaire completion and verification. All collected information was required to be authentic, complete, and verifiable against source documents.

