### Blinding

2.6

To further improve the effectiveness of the blind method, participants in both the AA group and the SAA group were uniformly informed that they needed to apply pressure after applying the skin-colored tape, thereby reducing patients’ sensitivity to group differences. Additionally, the skin-colored tape used in both the AA and SAA groups was identical in appearance and texture, and was fixed by researchers at the same ear acupoint locations, ensuring that they could not be distinguished visually. Participants, evaluators, and statisticians will remain blinded throughout the study to minimize potential bias arising from procedural differences. As acupuncturists are responsible for delivering the AA and SAA interventions, they cannot be blinded to group allocation; however, they will not participate in outcome assessments. Evaluators will remain fully blinded to group assignments. They will solely be responsible for data collection and are prohibited from discussing treatment-related information with participants.

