#### Secondary outcome

2.8.2

ASHS: A self-report measure assessing adolescents’ pre-sleep behavioral habits over the past month, including typical sleep routines and conditions, demonstrating robust psychometric properties (30). The scale consists of 28 items divided into 9 categories, with higher scores indicating better sleep hygiene. Categories include: Physiological domain (e.g., “I feel hungry when I go to bed”), Cognitive domain (e.g., “I go to bed thinking about things I need to do”), Emotional domain (e.g., “I feel anxious when I go to bed”), Sleep environment (e.g., “I fall asleep while watching TV”), Daytime sleep (e.g., “I nap for more than 1 hour during the day”), Substances (e.g., “I drink beer or other alcoholic beverages after 6 PM”), Bedtime (e.g., “I have a consistent bedtime”), Sleep stability (e.g., “I stay up later on weekends than my usual bedtime”), Bed/room sharing (e.g., “I sleep alone”)

CDI: CDI developed for children aged 6–16 years demonstrates good reliability and validity in Chinese pediatric populations (31), with participants selecting items that best describe their feelings over the past two weeks. The CDI consisted of 27 items divided into five dimensions: Anhedonia, Negative Mood, Negative Self-Esteem, Ineffectiveness, and Interpersonal Problem. Participants are asked to choose the item that best describes how they have felt in the past two weeks. Responses ranged from 0 to 2, indicating “often”, “occasionally”, and “always”, representing the frequency of occurrence, for a total score of 54. Lower scores indicate fewer depressive symptoms.

ASWS: The adolescent sleep quality self-report scale, clinically validated for reliability and validity (32), comprises 28 items designed to assess sleep quality in youth aged 12 to 18 years. Respondents are asked to rate the frequency of their sleep behaviors during the past month using a 6-point scale (ranging from “always” to “never”). Adolescent sleep is assessed across five behavioral dimensions: Bedtime (5 items), Sleep onset (6 items), Sleep maintenance (6 items), Sleep resumption (6 items), Waking up refreshed (5 items). An average subscale score for each dimension and a total sleep quality score (ASWS total score) can be obtained, with scores ranging from 1 to 6. Higher scores indicate better sleep quality.

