However, two critical research gaps persist: only two registered auricular acupressure trials target adolescents (ITMCTR2024000343, ITMCTR2100005080), while prospective preventive studies remain absent. This school-based intervention demonstrates feasibility through standardized protocols requiring minimal training, brief 5–7 minute sessions during breaks, and low-cost materials. The combined professional administration and parent-supervised home application ensures adherence without disrupting academics, offering a replicable model for educational settings.

This study used the Chinese version of the PSQI to evaluate adolescents’ sleep quality. the psycholemtric properties of the Chinese version of the PSQI have been validated in a large sample of 5,399 by Cheng (27). The scoring algorithm for the sleep duration item retained the original recommended hours for adults rather than reflecting the longer sleep needs of adolescents. Nevertheless, the findings from the confirmatory factor analysis supported a three-factor model, with configural and metric invariance across gender and age groups, indicating that the Chinese version of the PSQI is a valid and reliable measure of sleep quality in non-clinical adolescent populations.

This study also has some limitations. First, the study’s generalizability may be limited by its exclusive focus on secondary school students in Nanjing due to budgetary and staffing constraints, which could introduce selection bias. This may introduce selection bias. Second, this is a single-center design, and single-center trials often involve a homogeneous sample, limiting generalizability and potentially introducing experimental bias. Future studies should consider more influencing factors and further validate and explore the results in larger sample populations. Third, the study outcomes rely on self-report questionnaires, which, although widely used, may still be subject to subjective biases.

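### Section 2.11 brings parents, who supervise home treatment and can tell control from the taped arms, into completing and verifying the self-report questionnaires without keeping item answers private

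*Protocol article*

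**What the plan says.** Section 2.11 (Quality control) describes how the questionnaires are handled. It first states that "The PSQI, BDI, ASHS, ASWS, CDI and ASLEC scales will be assessed for completion eligibility by a professionally qualified physician". Later in the same paragraph it says that, for those who consented, "paper-based questionnaires were distributed, and parents/guardians were contacted to facilitate questionnaire completion and verification". No visit, list of scales or privacy arrangement is attached to that second statement.

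Other sections bear on it:

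- **Blinding (2.6)** lists who is masked: "Participants, evaluators, and statisticians will remain blinded throughout the study". Parents and guardians are not on the list. Of the evaluators it says: "They will solely be responsible for data collection and are prohibited from discussing treatment-related information with participants".
- **Interventions (2.7.1 to 2.7.3)** give the control group sleep hygiene education only. The AA and SAA groups receive ear tape as well, and the SAA tape holds no seeds.
- **Discussion (3)** describes the parents' part in treatment: "The combined professional administration and parent-supervised home application ensures adherence without disrupting academics". It also acknowledges that the outcomes are self-reported.
- **Data management (2.12)** restricts data access to approved researchers and requires the participant's written consent before anything goes to a third party.

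**The concern.** Both primary outcomes are the adolescent's own account of sleep and mood. Under 2.9, incident depression is counted from a BDI threshold, which 2.8.1 puts at 20 or more. Some secondary items are also sensitive within a family. The ASHS includes "I drink beer or other alcoholic beverages after 6 PM", and the ASLEC covers family conflict.

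A pupil who expects a parent to help with or check the form has a reason to understate low mood, conflict or drinking. Understatement common to all arms lowers the number of depression cases detected and dilutes any difference between arms. If the parent also knows whether the child is in a taped arm and has put effort into supervising treatment, the parent's expectations can enter the answers differently by arm. That is bias and not just lost sensitivity, and it would fall on the comparisons with control.

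**Working it through.** The article gives no figure on this point, so the check compares its statements.

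1. **Is the parents' role stated or inferred?** It is stated. Section 2.11 connects parents with both completion and verification. Whether they read or influence answers is not stated, but it is hard to see how a completed questionnaire could be verified without its content being seen.

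2. **Which scales?** The sentence names none. The paragraph it sits in names PSQI, BDI, ASHS, ASWS, CDI and ASLEC and no other instrument. The natural reading includes both primary outcomes, and nothing excludes them.

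3. **Which visits?** None is named. The sentence is in the past tense and follows the statement on consent, so baseline is a possible reading. However, it applies to consented participants, and section 2.1 gives the consent form to students who already meet the inclusion criteria, one of which is PSQI above 7 (2.2.1). Collection after consent therefore fits at least as well as screening. Tense is no guide, because the article mixes tenses throughout.

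4. **What do parents know of allocation?** Control pupils wear no tape and the other two groups do, so a parent can tell control from the taped arms. Between AA and SAA, section 2.6 says that "the skin-colored tape used in both the AA and SAA groups was identical in appearance and texture", and both groups are told to press. A parent could tell these two apart only by noticing the seeds, and the article does not say that this happens.

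5. **Does another section protect the answers?** Section 2.12 limits access to approved researchers, but does not say how this applies while a form is being completed or checked with a parent's help. Section 2.6 does not mention parents.

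6. **What follows under each reading of the visits?**
   - *Post-randomisation visits included:* under-disclosure can occur in all arms, and parental expectation can shift AA versus control and SAA versus control.
   - *Baseline only:* no answer can depend on allocation. Changing the conditions of completion between baseline and follow-up would still distort the paired pre-post tests in 2.9.1. It could also make depression concealed at baseline look new later.

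7. **Can the size be estimated?** No. The article gives no SD for the BDI, no rate of BDI of 20 or more among adolescents with insomnia, and no rate of non-disclosure. The 20% in the Introduction is for mild to moderate depression in adolescents generally. Applying it to 65 per arm would not estimate this endpoint in this sample.

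**The case against.** The strongest reply is that one loosely worded clause is being asked to carry too much. Contacting parents to facilitate completion could mean getting forms returned, chasing blanks or confirming medical history. A reader might infer that parents read or shape the answers at every visit, but the article does not say so, and the point does not rest on it. The baseline reading is also open, and 2.8.2 describes the ASLEC as a baseline assessment.

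A reader might also infer that 2.11 flatly contradicts 2.6, because evaluators there are solely responsible for data collection. That is not secure. The sentence may mean only that evaluators do nothing else. The tension with 2.12 is the firmer one.

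A third tempting inference is that parents are unblinded between AA and SAA. The tapes look identical, and any parental investment in supervision would apply to both arms.

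Two further replies carry weight. Control pupils know that they have no tape, so expectation bias against control exists whatever parents do. Section 2.10 also provides a professional depression assessment for all participants, so detecting depression does not rest wholly on the questionnaires. That assessment does not define the BDI outcome, however.

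Finally, an article may leave details of administration to the full protocol. That would answer a complaint about a missing detail. Here the article states a procedure that brings in a party outside the declared blinding, and that statement needs correcting or qualifying wherever the detail sits.

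**Conclusion.** The point holds as a risk created by the procedure as written. Parents who supervise treatment and can tell control from the taped arms are brought into completing and verifying questionnaires, in the paragraph that names both primary outcomes. The text neither restricts this to baseline nor keeps item answers from them.

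The likely consequences are under-disclosure of depressive symptoms in all arms and, if post-randomisation visits are covered, an additional expectation bias in the two comparisons with control. AA versus SAA is affected only if seeds are noticed. The documents do not allow the size to be estimated.

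The conclusion rests on two assumptions: that the sentence covers the scales named in its own paragraph, and that verification can expose answers. If parents in fact never see item answers, a clarifying sentence in 2.11 would be enough.

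**What to change.** Change 2.11 so that:

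- adolescents complete the self-report scales themselves at every visit, and no parent or guardian sees, helps with or verifies item answers;
- forms go directly, or in a sealed envelope, to the blinded evaluator, who checks completeness and resolves blanks with the adolescent;
- parents' involvement is limited to consent, reminders and factual items such as demographics and medical history.

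This brings 2.11 into line with the access limit in 2.12.

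The cost is small but not nil. Evaluators already collect the data. Time must still be found for the scales: five of them total 21 (BDI) + 28 (ASHS) + 27 (CDI) + 28 (ASWS) + 27 (ASLEC) = 131 items, plus the PSQI, at visits where all are used. The 5 to 7 minute break-time sessions in the Discussion are for treatment and should not be assumed to cover this. Sealed return allows completion elsewhere if school time is short, but gives less assurance of privacy than direct hand-over.

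The change does not remove the expectation bias that comes from control pupils knowing their own arm. It removes an avoidable second route.
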